### BLT and depression during pregnancy

The SCN generates the circadian rhythms in physiology and behaviour, including reproductive hormones. Pregnant women typically show disturbed, desynchronised circadian rhythms, resulting in disturbed sleep patterns, which puts them at risk for depression [39]. Moreover, disturbed sleep and decreased physical condition put pregnant women at risk for decreased activity and less exposure to daylight [40], which might further enhance their risk for depression.

Two small (*n* = 10 and *n* = 27) randomized controlled trials among pregnant women with non-seasonal depression showed significant improvement of depression among women exposed to BLT compared to placebo [41, 42]. Treatment effect in terms of mean improvement of depressive symptoms was comparable with the effects of antidepressant medication (effect size around 0.45), making it a competitive treatment for antepartum depression, but without the possible adverse effects of medication to the unborn child. Although these studies provide evidence for the effectiveness of BLT for depression during pregnancy, their sample size is small.

While in previous studies among elderly patients cortisol and melatonin rhythms normalized after BLT treatment [23], the question is whether improvement of depressive symptoms after BLT in pregnant women is also mediated through improved endocrine functioning or whether these symptoms are primarily determined by the physiology of pregnancy itself. Therefore, we will also examine the circadian rhythms and hormone levels of the pregnant women, to study whether BLT also effects endocrine functioning during pregnancy.

From previous research, we know that maternal depression during pregnancy negatively influences intra-uterine and postnatal child development [3–6, 43–47]. How intra-uterine child development is influenced by maternal depression has yet to be determined. Possible mechanisms are maternal cortisol crossing the placenta, placental secretion of CRH – which has a positive feedback loop with maternal and foetal cortisol – and reduced blood flow to the foetus, causing foetal growth restriction [5, 43–45, 47]. Increased maternal levels of cortisol, as a cause and/or consequence of maternal depression during pregnancy, might program the intra-uterine developing HPA-axis of the child, making it susceptible to increased stress reactivity in future life [3, 4, 48], which has also been confirmed in animal studies [49]. Therefore, where the earlier conducted studies on antepartum depression and BLT only studied the effects of BLT on mood [41, 42], it will be interesting to examine the effects on infant stress reactivity, long-term cortisol exposure and infant behaviour.

### Aims

In this study, we will primarily study the effects of BLT on depression during pregnancy, including adverse effects. Second, we will study whether this clinical improvement is accompanied by improved sleep quality and normalized melatonin and cortisol levels during pregnancy. Third, we will study the effects of BLT on gestational age, birth weight, infant behaviour, infant cortisol stress response and long-term cortisol exposure of the infant.

## Methods/Design

### Hypotheses

Primary hypothesis: Daily treatment with 6 weeks of morning BLT improves depressive symptoms during pregnancy.

Secondary hypotheses:Clinical improvement of depressive symptoms is accompanied by improved sleep patterns, lower basal cortisol levels and normalized melatonin concentrations during pregnancy.Treatment with BLT during pregnancy improves birth and child outcomes: higher gestational age, higher birth weight, less regulation problems in infants and lower cortisol stress response. In addition, infants will show lower long-term cortisol exposure.

### Study overview

This study is a randomized, double-blind, placebo-controlled clinical trial. After baseline measurements (T0), the participants will be randomly allocated to either receive active BLT or dim red light therapy (DRLT) in a 1:1 ratio. Subsequently, they will commence their daily treatment with light, which takes place at the participants’ home for 6 weeks. After treatment, follow-up will take place at the following time points:after 6 weeks of treatment, which marks the end of treatment (T1);3 weeks after end of treatment (T2);10 weeks after end of treatment (T3);at birth (T4);2 months postpartum (T5);6 months postpartum (T6);18 months postpartum (T7).

At these time points, questionnaires, body material and information from medical files will be collected (Table 1). A flowchart of this study is shown in Fig. 3.

**Table 1 Tab1:** Overview assessment of questionnaires and collection of body material and medical files per time point

	T0	IP ^a^	T1	T2	T3	T4	T5	T6	T7
Questionnaires									
SIGH-SAD	X	X	X	X	X		X	X	X
EPDS	X	X	X	X	X		X	X	X
Life events	X	X	X	X	X		X	X	X
PSQI	X	X	X	X	X		X		
User expectations	X								
User experiences			X				X		
MABS							X		
CBCL									X
Body material									
Urine cortisol	X		X	X			X		
Saliva cortisol/melatonin	X		X	X			X		
Hair cortisol	X				X		X		
Saliva cortisol (infant)							X		
Hair cortisol (infant)							X		
Actigraphy	X ^b^				X ^c^		X ^c^		
Collecting medical files						X			

*T0* baseline (start of treatment), *T1* after 6 weeks of treatment (end of treatment), *T2 = 3* weeks after treatment, *T3 = 10* weeks after treatment, *T4* birth, *T5* 2 months postpartum, *IP* intervention period, *SIGH-SAD* Structured Interview Guide for the Hamilton Depression Scale – Seasonal Affective Disorder version, *EPDS* Edinburgh Postnatal Depression Scale, *PSQI* Pittsburgh Sleep Quality Index, *MABS* Mother and Baby Scales, *CBCL* Child Behaviour Checklist

^a^In the intervention period, the questionnaires will be assessed weekly

^b^The actiwatch needs to be worn for 8 weeks at T0

^c^At T3 and T5, the actiwatch needs to be worn for 9 days

**Fig. 3 Fig3:**
[figure not shown]
Flowchart of overview study. DSM = Diagnostic and Statistical Manual of Mental Disorders; BLT = bright light therapy; DRLT = dim red light therapy

### Participants

In this study, pregnant women with a depressive disorder will be eligible for participation. The specific inclusion and exclusion criteria of the study are listed in Table 2.

**Table 2 Tab2:** Inclusion and exclusion criteria

Inclusion criteria	Women
	18–45 years of age
	12–18 weeks pregnant
	DSM-V diagnosis of depressive disorder (as assessed by the Structured Clinical Interview for DSM disorders)
Exclusion criteria	Insufficient proficiency in Dutch or English
	Multiple pregnancy
	The use of antidepressants shorter than 2 months
	Bipolar I or II disorder
	Any psychotic episode
	Substance abuse
	Primary anxiety disorder
	Recent history of suicide attempt
	Shift-work
	Somatic and/or obstetric conditions that override study participation
	Previous treatment with BLT
	Eye condition (macular degeneration, eye diseases, recent eye surgery)

### Recruitment

In the Netherlands, maternity care for low-risk pregnancies is provided in primary care, which is midwife-led. High-risk pregnancies are cared for in a general hospital (secondary care) or foetal-maternal medicine unit (tertiary care).

In this study, women will be mainly recruited through both midwifery practices and hospitals participating in the South West Consortium in the Netherlands. This is a unique consortium in which almost all parties involved in perinatal care in the South West region of the Netherlands are united: midwives, obstetricians, paediatrician, and several public health institutes. The consortium covers both urban areas (such as the city Rotterdam) and rural areas. Previous studies in this consortium involved screening for psychosocial risk factors, psychiatric disease and the impact of structuring psychosocial care. Rotterdam is the second largest city in the Netherlands with more than 620.000 inhabitants [50]. It has a high number of deprived neighbourhoods, defined as 10 % of pregnant women having a low socio-economic status (<20^th^ percentile) [51].

Women will be routinely screened on psychopathology and psychosocial problems during their first prenatal visit in midwifery practices and hospitals by a screening model, the Mind2Care [2]. During this screening, women are asked to fill out a web-based questionnaire, consisting of 33 items, covering four domains: a socio-demographic, obstetric, psychiatric and psychosocial domain, including the Edinburgh Postnatal Depression Scale (EPDS) [52]. A cut-off score of 9 or above of the EPDS is used by the Mind2Care, in order to refer a woman towards tailored mental health care. Sensitivity and specificity of the EPDS are respectively 86 and 78 % [52].

In addition, women who visit our outpatient psychiatric clinic – a centre of excellence in perinatal psychiatry – at the Erasmus University Medical Centre in Rotterdam for their depressive symptoms will be offered to participate in our study when they are not fully remitted from depressive symptoms after 2 months of treatment with antidepressant medication and/or other psychiatric treatment.

Third, pregnant women who visit their general practitioner (GP) for depressive symptoms may be referred to the study by their GP.

Finally, women will be recruited via (social) media, such as press releases, so women with depressive symptoms can enrol in the study without referral from their midwife, gynaecologist, GP or mental health care worker.

### Ethics

This study will be conducted in accordance with the Helsinki Declaration, meaning that participation is voluntary and written informed consent will be obtained. Before entering the study, subjects will receive information about the study and its risks and benefits, verbal and in writing. Subjects will have a reflection period of one week. Participants can leave the study at any time for any reason without consequences with regard to their current or future treatment. Also, the investigator can decide to withdraw a participant from the study for urgent medical reasons.

The study has been approved by the medical ethical committee of the Erasmus University Medical Centre, Rotterdam, The Netherlands (registration number MEC-2015-731). A Data Safety Monitoring Board has been installed, which monitors the safety of this research.

In case of adverse effects, a treatment protocol will be effective.

### Intervention

Participants will be randomly allocated to BLT (9.000 lux) or DRLT (100 lux). Treatment will take place daily at home for 6 weeks, starting at 12–18 weeks pregnancy. Participants will be asked to commence the treatment within 30 min of habitual wake-up time with a duration of 30 min. Participants will sit in front of two light boxes with a distance of approximately 40 cm. The light boxes will be placed in a custom-made scaffolding. In this way, the height of the light boxes can be adjusted per person, ensuring the same distance. Also, the scaffolding ensures lighting from above, which avoids glare [42]. This makes the treatment more comfortable, enhancing treatment adherence.

The active dose was found effective in other studies [23, 41, 42]. Dim red light can be considered to be biologically inactive [55]. Although a Cochrane review of studies in BLT in non-seasonal depression showed that BLT may be effective in as little as 1 week [55], we will choose 6 weeks of daily light exposure, since the 2 studies among pregnant women with non-seasonal depression showed significant effects of BLT from 5 weeks treatment [41, 42].

All participants in both treatment arms will receive treatment as usual. Women are always free to visit their GP, whenever they are in need of this. The GP is always free to start treatment if he/she feels necessary.

When depressive symptoms increase and/or in the case of suicidal ideation, an action plan is set up and appropriate measures will be taken.

Different measures have been taken to enhance treatment adherence:A sensor that measures the amount of lux perceived is installed in the actiwatches, which will monitor the therapy adherence.Since the lamps will be installed into a custom-made scaffolding that ensures lighting from above, treatment will be more comfortable, which enhances treatment adherence.

### Outcome measures

The primary outcome measure will be the average change in depressive symptoms between the two groups, as measured by the Structured Interview Guide for the Hamilton Depression Scale – Seasonal Affective Disorder version (SIGH-SAD) and the EPDS at different time points. Second, we will study responders vs. non-responders, where response is defined as a ≥50 % decrease to a final score of ≤ 8 on the 17-item Hamilton scale and ≤ 5 on the EPDS.

The secondary outcome measures of this study will be the changes in maternal cortisol and melatonin levels (1), in maternal circadian rhythm (2) and in birth and child outcomes (3).Morning and evening cortisol levels in saliva will be measured as a measure for HPA-axis activity. Morning and evening melatonin levels in saliva will be measured as measure of a participant’s circadian phase position. Outcome measures will be the changes in cortisol and melatonin saliva levels between the two groups.Total 24-h cortisol excretion will be determined from urine. Outcome measure will be the changes in cortisol levels within and between the two groups.Hair will be used as a long-term measure for cortisol excretion. Changes in levels between the two groups will be used as outcome measure.Through actiwatches and a structured questionnaire (the Pittsburgh Sleep Quality Index – PSQI), information will be obtained regarding total sleep time, sleep efficiency and sleep onset latency, as well as circadian estimates from the rest activity rhythm such as intradaily and interdaily variability and rhythm amplitude.Differences in birth and child outcomes between the two groups will be used as outcome measures: pregnancy duration, birth weight, child behaviour, long-term cortisol exposure and cortisol stress response at a routine vaccination.

Finally, we will ask about user expectations and user experiences.

Complete follow-up will be pursued. In case of discontinuing or deviating from the intervention, we will collect outcomes of EPDS and SIGH-SAD assessment.

### Sample size

Based on previous literature [23, 41, 56], we expect a small to moderate response (time x treatment interaction on depressive symptoms). This corresponds to a 10 to 15 % reduction of depressive symptoms over the full course of treatment. To demonstrate this (with an α of 0.05 and a β of 0.80), we will need a sample size of 63 participants per arm (126 in total). To account for lost to follow up during and after treatment, we will aim at including 150 participants. Power calculations were performed using GLIMMPSE 2.1.5 software [57].

In case of withdrawal of a participant during the recruitment period, another participant will be recruited to obtain the aimed number of participants.

### Adverse effects

At every measurement, we will ask for adverse effects. The adverse effects of BLT, such as headache and nausea, are generally mild and short-lived [58, 59]. A switch to hypomania is a more serious adverse effect, which would require effect managing. In a study exploring the side effects of short-term 10,000 lux light therapy in 70 patients suffering from SAD, 1 subject experienced hypomania [58]. In the two studies (*n* = 10 and *n* = 27) studying the effects of light therapy in a pregnant population, 1 subject showed hypomanic symptoms [41, 42]. If a participant shows hypomanic symptoms, the daily treatment duration will be reduced. This enhances the clinical safety [41].

No adverse effects for the foetus will be expected [42, 56].

### Measurements

#### Primary outcome measures

Depressive symptoms during pregnancy will be assessed using the SIGH-SAD and the EPDS.

### SIGH-SAD

The SIGH-SAD is a 29-item structured interview and consists of 21 HAM-D (Hamilton Rating Scale for Depression) items and 8 atypical items, of which 11 items can be scored with a value of 0–2, 5 items with a value of 0–3 and 13 items with a value of 0–4 [61]. The sum score ranges from 0 to 63 for the HAM-D items and from 0 to 26 for the atypical items, resulting in a total sum score of 0 to 89 [61].

We will choose the original 17-item HAM-D questionnaire as primary measure, since it is more commonly used in clinical practice and research. Interrater reliability for the 17-item HAM-D questionnaire ranges from 0.82 to 0.98 [62]. Sensitivity and specificity are respectively 0.76 and 0.91 [62]. Positive and negative predictive value are respectively 0.77 and 0.92 [62]. Next to the original 17-item HAM-D questionnaire, we will use the entire SIGH-SAD questionnaire, since this questionnaire is the current benchmark for assessment of severity of depression in light therapy trials.

### EPDS

The EPDS, a structured 10-item questionnaire, will be used as a validated self-report measure of depression during pregnancy [52, 63]. Each item is scored with a value, ranging from 0 to 3, which leads to a sum score of 0 to 30 [52]. Sensitivity and specificity of the EPDS are respectively 86 and 78 % [52]. Originally, the EPDS was developed for the detection of postnatal depression, but has been validated for screening depression during pregnancy as well [63]. In this study, we will use a cut-off of 9, in accordance with the screening tool, the Mind2Care [2].

#### Secondary outcomes (endocrine)

Endocrine levels during pregnancy will be studied measuring saliva melatonin and cortisol in urine, saliva and hair.

### Urinary free cortisol

Urinary free cortisol levels during a 24-h period provide a non-invasive valid estimation of overall daily cortisol production [64]. Urine will be collected starting after the first voided urine after awakening and will include the first voided urine on the following day. The cortisol level will be determined by radioimmunoassay. Completeness of collection will be ascertained by interviews documenting urine losses. Only complete collections, with creatinine within the normal range of 0.06 mg/dL per 24 h will be included in the analysis.

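### The creatinine rule for admitting 24-hour urine collections is one value in an incoherent unit and cannot be applied as printed

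*Protocol article*

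**What the plan says.** The protocol article lists 24-hour urinary cortisol among the secondary outcomes. Outcome measures states: "Total 24-h cortisol excretion will be determined from urine", with changes compared within and between the groups. In Table 1 (Study overview) the row "Urine cortisol" is marked at T0, T1, T2 and T5.

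The section Urinary free cortisol sets two conditions for using a collection. The first is an interview: "Completeness of collection will be ascertained by interviews documenting urine losses". The second is a creatinine threshold: "Only complete collections, with creatinine within the normal range of 0.06 mg/dL per 24 h will be included in the analysis".

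No other part of the article gives a lower limit, an upper limit, a tolerance, a direction or a source for the creatinine figure.

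**The concern.** The sentence decides which urine collections are analysed, and it has two defects that can be seen without any outside source.

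- It calls a single number a range. It does not say whether 0.06 is a floor, a ceiling or a target.
- Its unit, mg/dL per 24 h, is not a quantity that a laboratory can report for a 24-hour collection. A concentration is in mg/dL. An excretion is in mg or mmol per 24 h and equals concentration times volume.

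Someone will have to replace the rule before urinary cortisol can be analysed. If that is done after the results are known, the choice of limits also decides which observations count. Three of the four time points (T1, T2, T5) come after randomisation, and T0 is the baseline from which change is measured.

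**Working it through.** **The plan's own figure.** It cannot be reproduced. The article gives no urine volume, no creatinine distribution and no reference range from which 0.06 could have been derived. What can be done is a check of units and a check of scale.

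**Inputs**

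- From the article: the threshold, "normal range of 0.06 mg/dL per 24 h".
- Assumed, not in the article: urine volume 0.5 to 3 L (5 to 30 dL) per 24 h.
- Assumed, not in the article: creatinine excretion 500 to 2000 mg per 24 h.

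**Unit check.** Excretion (mg per 24 h) = concentration (mg/dL) × volume (dL per 24 h). The printed unit is neither the left side nor either factor on the right. Taken strictly, no measured quantity can be compared with it.

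**Scale check, reading 0.06 as a concentration and ignoring the words on time**

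- Excretion implied at 5 dL: 0.06 × 5 = 0.3 mg per 24 h.
- Excretion implied at 30 dL: 0.06 × 30 = 1.8 mg per 24 h.
- Lowest concentration under the assumptions: 500 / 30 = 16.7 mg/dL, which is 16.7 / 0.06 ≈ 280 times the printed figure.
- Highest concentration under the assumptions: 2000 / 5 = 400 mg/dL, which is 400 / 0.06 ≈ 6,700 times the printed figure.

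**Scale check, reading 0.06 as a mass and ignoring the dL.** 500 / 0.06 ≈ 8,300 and 2000 / 0.06 ≈ 33,300. Dropping either half of the unit therefore does not rescue the number.

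**What the rule would do, with concentrations between 16.7 and 400 mg/dL**

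| Reading of 0.06 mg/dL | Collections excluded |
|---|---|
| Exact value (0.055 to 0.065 after rounding) | essentially all |
| Upper limit | all |
| Lower limit | none |

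One sentence thus permits analysis sets from about 0% to about 100% of collections.

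**Comparison within the article.** The neighbouring validity rules can be applied as written: at least 6 valid samples in a day for saliva cortisol, and 3 valid evening samples for melatonin. The difficulty is confined to the urine rule.

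**The case against.** Several arguments limit the point, and most of them stand.

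- **A reader might infer that the rule would discard essentially every collection and leave no data.** The document does not support that. It follows only if 0.06 is an exact value or an upper limit. A lower limit is a plausible form for a completeness check, and on that reading almost nothing is lost. If the unit is taken strictly, the rule yields no inclusion percentage at all.
- **A reader might also put the error at about 1,000-fold.** That rests on assumed volumes and excretion. The assumptions used here give about 280 to 6,700 when the figure is read as a concentration, and no single factor can be derived from the article.
- **The article has a second completeness check.** The interview on urine losses works without the creatinine figure, so the whole completeness procedure is not broken. But creatinine is written as a further condition for inclusion, and the interview does not tell the analyst how to apply it.
- **The reach is small.** Maternal cortisol is also measured in saliva and hair, and the hypothesis of lower basal cortisol names no specimen.
- **Bias is not shown.** The participants, the assessors and the researcher doing the primary analysis are blinded, and nothing suggests that a corrected limit would favour one arm. The statement about the analyst does not expressly cover secondary analyses, however, so the opening remains.
- **The text may have lost a character when it was read from the PDF.** This cannot be excluded, but nothing in the sentence shows it and dashes in ranges survive elsewhere. A lost dash or digit would not explain the mixed unit.

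Laboratory detail is often left to a fuller document. Here, however, the article states a threshold, and states it in a form that cannot be used.

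**Conclusion.** Wrong as written; minor severity. The single value and the incoherent unit can be verified from the sentence itself and need no assumption. The consequence is an undefined analysis set for one secondary outcome at four time points. The span from nearly all to nearly none excluded depends on the assumed volumes (0.5 to 3 L) and creatinine excretion (500 to 2000 mg per 24 h), together with the reading chosen. The document does not establish that the urinary data would be lost, nor that the result would be biased. The primary outcome and the saliva and hair measures do not depend on this rule.

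**What to change.** Replace the figure with a lower and an upper limit of total creatinine excretion per 24 h, calculated as concentration times recorded volume and expressed in mg or mmol per 24 h. Take the limits from the laboratory's reference, state that source, and fix them before unblinding. The article does not contain the information needed to derive the limits, so no values are offered here.

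Optionally, report a sensitivity analysis that includes all collections judged complete by interview, to show whether the creatinine condition matters to the result.

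The cost is one corrected sentence and a query to the laboratory. The rule already presupposes that creatinine is measured; total excretion also needs the volume of each collection to be on record. The optional analysis adds one further run of the same model.
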